## Abstract

**Background:**

Globally, COVID-19–related psychological distress is seriously eroding health care workers’ mental health and well-being, especially in low-income countries like Nigeria. The use of mobile health (mHealth) interventions is now increasingly recognized as an innovative approach that may improve mental health and well-being. This project aims to develop an mHealth psychological intervention (mPsyI) to reduce COVID-19–related psychological distress among health care workers in Nigeria.

**Objective:**

Our objective is to present a study protocol to determine the level of COVID-19–related psychological distress among health care workers in Nigeria; explore health care workers’ experience of COVID-19–related psychological distress; develop and pilot test mPsyI to reduce this distress; and assess the feasibility of this intervention (such as usability, engagement, and satisfaction).

**Methods:**

A mixed (quantitative and qualitative) methods approach is used in which health care workers will be recruited from 2 tertiary health care facilities in southwest Nigeria. The study is divided into 4 phases based on the study objectives. Phase 1 involves a quantitative survey to assess the type and levels of psychosocial distress. Phase 2 collects qualitative data on psychosocial distress among health care workers. Phase 3 involves development of the mHealth-based psychological intervention, and phase 4 is a mixed methods study to assess the feasibility and acceptability of the intervention.

**Results:**

This study was funded in November 2020 by the Global Effort on COVID-19 Health Research, and collection of preliminary baseline data started in July 2021.

**Conclusions:**

This is the first study to report the development of an mHealth-based intervention to reduce COVID-19–related psychological distress among health care workers in Nigeria. Using a mixed methods design in this study can potentially facilitate the adaptation of an evidence-based treatment method that is culturally sensitive and cost-effective for the management of COVID-19–related psychological distress among health care workers in Nigeria.

**International Registered Report Identifier (IRRID):**

DERR1-10.2196/36174

## Introduction

Globally, medical doctors and nurses have been praised for their dedication in providing care for those affected with SARS-CoV-2, responsible for the ongoing COVID-19 pandemic. The frontline occupied by medical doctors and nurses in the fight against COVID-19 has had a heavy toll on their mental health [1]. A high prevalence of COVID-19–related psychological distress among medical doctors and nurses has been reported in Nigeria [2,3].

Psychological interventions targeting medical doctors and nurses are very important, as they comprise a high-risk group for COVID-19–related psychological distress [4]. Moreover, mobile health (mHealth) interventions are increasingly seen by some experts as a game changer in the context of solutions to mental health and well-being challenges [5,6]. mHealth describes various health care practices and delivery based on apps or software installed on mobile devices, such as smartphones or phablets, client supervising and monitoring devices, and personal digital assistants [7]. The concept of mHealth also pertains to using these devices to synthesize and store data as well as retrieve and exchange information among those connected to the mHealth platform [8]. The provision of medical and public health services through mHealth is dependent primarily on the mobile phone use of SMS text messaging, voice, and multimedia services [9].

In achieving universal health coverage, mHealth can broaden health care services’ quality and reach and enhance human resources’ capacity [10]. Due to the widespread usage of smartphones, mHealth apps are an increasingly acceptable avenue for implementing interventions for psychological or mental health problems [11]. One significant advantage of the mHealth technology is its capability for periodic sampling and recording the prevailing behaviors and experiences of the users in real time and in natural settings; this is described as ambulatory assessment or experience sampling method [12]. mHealth-based ambulatory assessment can also be applied with psychological or behavior change interventions, a concept described as ecological momentary interventions whereby treatment is provided to subjects in real-time contexts and settings [13]. These treatments can be administered independently or as a supplement to other ongoing treatments. The use of mHealth interventions has been described as a “therapist in the pocket” treatment technique and is extensively perceived to have the capability to transform psychological treatment [14].

Nigeria, the seventh most populous country globally, has an estimated population of 203 million [15] and has the most extensive and fastest-growing mobile phone market on the African continent [16]. Currently, the use of smartphones in Nigeria is approximated at 40 million, and it has been projected to increase to 140 million by the year 2025 [17]. The use of smartphones has been described as universal among Nigerian doctors and nurses [18]. Although a study reported that a significant percentage of Nigerian medical doctors and nurses were not familiar with the term “mHealth,” most are aware of the application of mobile phones in health care and delivery [19]. A systematic review that evaluated mHealth interventions targeted at health care workers reported that these interventions focused primarily on patient data collection during hospital visits, facilitation of communication between health care workers and patients, interactions between health care workers, and public health monitoring [20].

A literature search revealed that no study had described an mHealth-based intervention protocol directly targeted at reducing COVID-19 pandemic–related psychological distress among Nigerian health care workers, specifically medical doctors and nurses. Most of the empirical evidence for the use of mHealth interventions to improve the mental health of health care workers are from the high-income countries such as Spain [21,22]. The authors of an mHealth-based intervention to reduce mental health problems among Spanish health care workers during the COVID-19 pandemic indicated that additional mHealth treatments specifically tailored to improving the mental well-being of health care workers are needed [21]. However, this intervention was mostly beneficial to participants who were also receiving medication and psychotherapy and may reflect the short duration of the intervention—2 weeks. A meta-analysis of randomized clinical trials of psychological interventions delivered through mHealth for anxiety [23] and depressive [24] symptoms in a general population sample reported statistically significant reductions in symptom severity among those exposed to the interventions as compared to the control group.

Due to the impact of the COVID-19 pandemic on the mental health and well-being of health care workers, we acquired funding to develop or adapt and evaluate the feasibility (ie, usability, engagement, satisfaction, acceptability, benefits, and challenges) of an mHealth-based psychological intervention (mPsyI) specifically for medical doctors and nurses in Nigeria. This intervention is a subjectively managed and subjectively guided psychoeducation mobile-based treatment app that does not require the support of a therapist to ease the symptoms of psychological distress (ie, anxiety and depressive symptoms). This paper presents the description of the protocol for a study on developing the mPsyI app, in conformity with the Standard Protocol Item: Recommendations for International Trials (SPIRIT) guidelines [25]. The overall aim of the study is to investigate COVID-19–associated psychosocial distress and evaluate the feasibility of using the mHealth-based intervention in managing this distress among health care workers in Nigeria. The specific objectives are to assess the type and level of psychosocial distress associated with COVID-19 among health workers in Nigeria; explore health care worker’s experience of psychosocial distress associated with COVID-19; develop an mHealth-based guided psychological intervention; and assess the feasibility of the intervention.

## Methods

### Study Setting

The target population comprised doctors and nurses working in the following 2 tertiary hospitals in southwest Nigeria: the Obafemi Awolowo University Teaching Hospital Complex (OAUTHC) in Ile-Ife and the Lagos State University Teaching Hospital (LASUTH) in Lagos. The 2 hospitals were chosen because of ease of access, similar health care delivery structures, and minimal cultural differences. OAUTHC is a Federal Government–owned tertiary hospital with 465 doctors and 887 nurses, and LASUTH is a State Government–owned tertiary hospital with 536 doctors and 987 nurses.

### Design

The study will employ a mixed methods (quantitative and qualitative) approach.

### Recruitment

At the beginning of study phases 1 and 2 (explained below), electronic advertisements including links to the survey were broadcast on professional social media platforms used by health workers in OAUTHC and LASUTH, Nigeria, such as WhatsApp groups, Facebook, email lists, and departmental noticeboards. The advertisements were rebroadcast 3 times a week for the duration of each study period or until the optimal sample size was attained. These were supplemented by physical advertisements placed on departmental noticeboards in the hospital. Participants could follow links in these advertisements to the participant information sheets for both study phases. The sheets contained the aims and scope of the study, the contact details of the principal investigator for further enquiries, and a web-based form to provide contact details for prospective participants in the qualitative studies (to help research assistants contact participants); consent for the web-based survey was obtained by asking participants to select a button indicating this on the survey.

### Sample Size

Phase 1 (quantitative study) comprised 440 nurses and doctors (ie, health care workers), derived using the sample size formula for estimating population proportions using 38.5% as the proportion of health care workers with psychiatric morbidity, based on previous work among Nigerian health care workers [26]. We estimated a minimum sample size of 364 to give a power of 80%, and this was increased by 20% to 440 to allow for incomplete data. Phase 2 (qualitative study) comprised 60 in-depth interviews and 20 key informant interviews and 4 focus group discussions (24 participants). Analyses were carried out alongside data collection to enable us to detect saturation and discontinue subsequent interviews. In phase 4 (mixed methods study), 40 participants will be purposely selected for an in-depth interview.

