### Statistical Analysis

The recorded interviews will be transcribed verbatim and uploaded into the NVivo 12 for analyses using the framework approach [38]. The framework approach involves 3 interconnected steps that include familiarization with the transcript, deciding initial themes or categories, and summarizing or synthesizing the data [39]. For quantitative data, statistical analyses will be performed using the IBM-SPSS software for Windows (version 27; IBM Corp). Descriptive statistics, frequency distributions, and percentages will be used for categorical variables. For continuous variables, mean, median, standard deviation, percentiles, and ranges will be used. Between-group percentages will be compared with chi-square tests for observed differences, and the student *t* test will be used to determine differences in scores in different groups. Bivariate relationship will be investigated using Pearson correlation, and multiple regression analyses will be used to examine the relationship between psychological distress and the independent variables. Statistical significance will be based on 2-sided tests and set at *P*<.05.

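### The Phase 1 minimum of 364 comes from a precision formula, so the 80% power attached to it is unsupported and should be restated as a confidence interval width

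*Protocol article*

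**What the plan says.** The Sample Size section of the protocol article says that the Phase 1 size was "derived using the sample size formula for estimating population proportions", "using 38.5% as the proportion of health care workers with psychiatric morbidity". The next sentence gives the result and a property of it: "We estimated a minimum sample size of 364 to give a power of 80%, and this was increased by 20% to 440", the increase being an allowance for incomplete data. The section gives no confidence level, margin of error, null value, effect size or comparison for this calculation, and no expected rate of incomplete responses.

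The Procedure section describes Phase 1 as a survey of the type and level of distress, which is a descriptive aim. The Statistical Analysis section adds tests: "Between-group percentages will be compared with chi-square tests for observed differences", together with t tests, correlation and multiple regression. It fixes the error rate in these words: "Statistical significance will be based on 2-sided tests and set at" P<.05.

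**The concern.** A formula for estimating a proportion takes a confidence level, an assumed proportion and a margin. It has no alternative hypothesis, so power cannot come out of it. The article names such a formula and then reports a power.

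The stake is interpretation. The 80% is the only power figure in the article, and hypothesis tests are planned at a two-sided 5% level. A reader may attach the 80% to those tests and take a non-significant group comparison as adequately powered evidence of no difference. The phrase could also be carried into the Phase 1 report, which the Results section says is under review at a journal.

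**Working it through.** **Inputs**

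- From Sample Size: p = 0.385, so p(1−p) = 0.385 × 0.615 = 0.236775; minimum 364; increase of 20% to 440.
- From Study Setting: staff of 465 + 887 + 536 + 987 = 2875.
- From Statistical Analysis: two-sided 5% tests.
- Assumed, because not stated: 95% confidence (z = 1.96) and a margin d of 0.05, with 0.03 to 0.07 tried.

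**1. Reproduce 364.** The precision formula is n = z² p(1−p)/d². It gives 1.96² × 0.236775 / 0.05² = 363.8, so 364. At the same confidence level, margins of 3, 4, 6 and 7 points give 1011, 569, 253 and 186, so of the margins tried only 5 points returns the stated figure. A finite population correction gives 363.8 / (1 + 362.8/2875) = 323.1, so the stated figure does not include one.

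**2. Add a power term.** A one-sample test against 38.5% with 80% power needs n = (1.96 + 0.842)² p(1−p)/d². At d = 0.05 this is 744, or about 730 to 752 if the variance under the alternative is used, depending on direction. That is about twice 364, so 364 did not come from this calculation at a 5-point difference.

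**3. Power that 364 does give.** The standard error is √(0.236775/364) = 0.0255.

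- For a 5-point difference: 0.05/0.0255 − 1.96 ≈ 0, so power is about 50%. This follows from the construction, because the margin was set at 1.96 standard errors.
- For 80% power: (1.96 + 0.842) × 0.0255 = 0.071, a difference of about 7 points. The article names no such difference.

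**4. Precision.** The 95% half-width is 1.96 × √(0.236775/n).

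| Complete responses | Half-width (points) |
|---|---|
| 364 | 5.00 |
| 440 | 4.55 |
| 352 | 5.08 |

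**5. The increase to 440.** 364 × 1.20 = 436.8, rounded up to 440, so the stated arithmetic is right. The break-even incomplete rate is 1 − 364/440 = 17.3%. If 20% of 440 were incomplete, 440 × 0.80 = 352 would remain. With a finite population correction for 2875 staff, the half-width at 352 is 5.08 × √((2875 − 352)/2874) ≈ 4.8 points.

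**The case against.** The strongest defence is that nothing in the design fails. The size is correctly derived for a prevalence survey, the aim is descriptive, and the Statistical Analysis section does not tie the 80% to any test. Recruitment ended in August 2021, and the 40 participants of Phase 4 are justified separately. All of this stands, and it limits the point to a correction of wording. It does not rescue the power phrase. A condensed article may leave the margin and confidence level to a fuller document, but here it states a property that its named formula cannot supply.

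Three stronger readings are tempting, and the document does not support them.

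- A reader might infer that the 80% is simply false. The power is undefined, since no effect is given, and 364 does have 80% power for some unstated difference (about 7 points from 38.5%). Unsupported, and contradicted by the named formula, is as far as the text allows.
- A reader might infer that the increase to 440 is an error and that 364/0.80 = 455 are required. The article gives 20% as the size of the increase and states no expected loss, so no loss assumption of its own is broken. Even if 20% is read as a loss rate, the change in half-width is 0.08 points and disappears once the finite staff population is taken into account.
- A reader might put a figure on the power of a doctor-nurse comparison. If responses split in the staff ratio (1001 to 1874), 80% power corresponds to a gap of about 15.0 points at 364 and 13.6 at 440. The article specifies neither that comparison nor that split, so these figures illustrate the issue and are not a finding.

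**Conclusion.** The point holds as a mismatch between method and claim. The article describes a precision calculation and labels its result with a power that the calculation does not contain. The size of the discrepancy is about 50% power, against the stated 80%, for a difference equal to the inferred 5-point margin; 80% power at that difference would need about 744 responses. This rests on the inferred 95% level and 5-point margin, which return 364 exactly. That the formula has no power term does not depend on those two values.

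The sample size is adequate for estimating prevalence. The point about the increase is secondary and conditional: it matters only if 20% was meant as the expected incomplete rate, and then only slightly.

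**What to change.** In Sample Size, delete the words that attach a power of 80% to 364. In their place, after confirming the confidence level and margin used, write: *364 complete responses estimate a prevalence of 38.5% with a 95% confidence interval half-width of 5 percentage points (about 4.5 points with 440). The size was not based on power for the between-group tests described under Statistical Analysis.*

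State also whether 20% is only the size of the increase or the expected incomplete rate. If it is the expected rate, add that about 352 complete responses would remain, with a half-width of about 5.1 points, or about 4.8 with a finite population correction for 2875 staff.

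Make the same correction in the Phase 1 report if the power phrase appears there. The cost is wording only: there is no extra enrolment and no change to the analysis.

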### Procedure

The study was divided into 4 phases as follows: in the first phase, a quantitative survey will be conducted among health care workers to assess the type and levels of psychosocial distress. The second phase involves qualitative data collection (ie, in-depth interviews, key informant interview, and focus group discussions) among health care workers. In the third phase, a modified Delphi panel comprising a group of experts will be conducted to develop the mHealth-based psychological intervention according to an available evidence-based intervention tool kit [6,27], and the fourth phase is a mixed methods study to assess the feasibility and acceptability of the mHealth-based guided psychological intervention.

#### Phase 1 (Quantitative Survey)

In this phase, doctors and nurses from the 2 hospitals who consented to participate in the study were requested to complete the following measures: The Kessler Psychological Distress Scale [28], the 9-item Patient Health Questionnaire [29], the 7-item Generalized Anxiety Disorder scale [30], the Short Adapted Social Capital Assessment Tool [31], and the Social Connectedness Scale-Revised [32].

These questionnaires were administered physically, and the responses built into electronic forms using REDCap (Version 11.1.2). Only one entry was allowed per participant for the web-based survey. After completing the survey, we asked participants interested in follow-up studies (phase 2) to provide their contact details, which were stored separately from their provided data. To ensure sociocultural relevance, the variables were selected based on previous research among Nigerians, which showed that pandemic-related stress was associated with higher anxiety and depressive symptoms and perceived social support was protective against these adverse mental health outcomes among Nigerians [33].

#### Phase 2 (Qualitative Study)

The aim was to explore health care workers’ experience of COVID-19–associated psychosocial distress and available psychosocial support in their workplace. It comprised 60 in-depth interviews, 20 key informant interviews, and 4 focus group discussions. Previous qualitative studies have recommended a minimum sample size of at least twelve to reach data saturation [34,35]. Through the interviews, we contextualized and understood the experience of psychological distress associated with the COVID-19 pandemic among health care workers; identified protective factors and available psychosocial support at their workplace; and explored the desired features and preferences for an mHealth-based psychological intervention as well as potential barriers to intervention delivery. The in-depth interviews and key informant interviews were conducted through telephone calls and physical meetings (the recommended social distancing measures by the World Health Organization and appropriate personal protective equipment were used). Interview guides were developed, and all interviews were conducted in English, audio recorded, and transcribed for analyses.

#### Phase 3 (Intervention Development)

This phase aims to develop gender-related and culturally sensitive aspects of the mHealth guided psychological intervention. Results from phase 1 will provide quantitative data, and phase 2 will provide qualitative data, such as the expression of psychological distress among Nigerian health care workers. Phase 2 will inform the sociocultural adaptation of available evidence-based psychological interventions [6,27]. Specifically, themes that emerge from phase 2 will be used to contextualize the intervention by changing phrases in the intervention in a more culturally appropriate way and using culturally relevant examples to make it more relevant to the lived experiences of Nigerian health care workers. Both male and female Nigerian voices will be used in the oral or spoken draft of the mPsyI intervention.

A modified Delphi approach (carried until saturation is achieved) will be conducted among a panel of experts in psychiatry, clinical psychology, guidance and counselling, nursing, and computer science. An intervention will be identified based on the World Health Organization collection of low-intensity psychological interventions [6,27]. This intervention will be independently scored for feasibility (ie, usability, engagement, satisfaction, acceptability, benefits, and challenges) using a 5-point scale. The experts will later decide on intervention options based on brevity, cost, the best mode of delivery, and the total number of sessions and then produce an initial draft of the mPsyI intervention. The initial oral or spoken draft of the mPsyI will be presented to end users (ie, health care workers with psychological distress) and facilitators (ie, health care workers without significant psychological distress or professional qualifications in mental health) to assess the practical application, usefulness, and feasibility of the proposed intervention and give feedback via questionnaires (ie, the System Usability Scale and the Mobile App Rating Scale, described below) and informal interviews. Both groups will suggest possible improvements and modifications of the intervention, including the language and contents of the intervention package, during discussions. These suggestions will be returned to the Delphi panel, who will then produce an amended draft of the mPsyI intervention tool kits, including manuals, training guidelines, as well as monitoring and evaluation methods.

